## Safety Analyses for Clinical and Laboratory Measurements

The rate of severe reactions will be used as the primary measure of clinical safety of this study drug. Assessment of product safety will include clinical observation and monitoring of hematologic and chemical parameters. All participants will be monitored for local and systemic adverse reactions during the course of the trial. Participants will be closely monitored for the first 8 weeks after product dispensation and followed for at least 15 months on product.

Adverse experiences will be coded into MedDRA (Medical Dictionary for Regulatory Activities) preferred terms. The number and percentage of participants experiencing each specific adverse experience will be tabulated by severity and relationship to treatment. Overall summaries by treatment will include the number and percentage of participants experiencing: (1) an adverse experience; (2) any moderate, severe, or life-threatening experience; (3) any severe or life-threatening experience; (4) adverse experience judged possibly related, probably related, or definitely related to treatment. Additional summaries will summarize the effect of adverse events on study drug dosing. A separate tabulation of SAEs will also be generated and will provide details including severity, relationship to treatment, onset, duration, and outcome. Adverse events that lead to product or study discontinuation will be listed separately.

Participants who become HIV-1 infected while on study will be monitored in a second part of the protocol (Part B). Both potential benefits and potential detrimental effects of the study product based on secondary endpoint analyses described above will be investigated. Clinical endpoints (major and minor) associated with the disease progression (e.g., setpoint, resistance,) will be recorded. Because few clinical endpoints are expected to be observed to support a quantitative analysis, qualitative case-descriptions will be done.

Three types of safety analyses will be performed depending on the outcome of interest as described in the next three sections. All safety analyses described will be adjusted for study site and the delayed /immediate treatment group variable. It will be explored whether these factors modify (i.e., effect modifiers) any of the observed outcome – treatment relationships and whether study drop-outs are comparable to either a) all others still on study (missing completely at random) or b) to others still on study within their site by study group (missing at random).

## Safety Analyses for Behavioral Outcomes

Data will be collected on HIV risk behaviors at enrollment and 3-month intervals throughout the study to assess the behavioral safety of study product use. The main behavioral safety analysis will compare the overall level of selected behaviors in the immediate and delayed treatment arms over the first nine months of the study. Statistical analyses for dichotomous (yes/no) responses will account for the within-individual correlation using longitudinal binary regression models. The study will have good power (>80%) to detect differences in the probability of a yes response between the groups of 12% or more assuming that the probability of a yes response in the delayed group is 28% or greater. All analyses will account for within-individual correlation using longitudinal models for continuous variables (e.g. Poisson outcomes). Subsequent analyses will examine whether there is a trend in the difference of a yes response between the two groups over time and trends in the probability of a yes-response within both the TDF and placebo groups while on study product. This last analysis will also be examined in relation to an individual’s perception that they have been randomized to a TDF group.

In all analyses, study drop-outs will be evaluated to assess their comparability to either a) all others still on study (missing completely at random) or b) to others still on study within their site by study group (missing at random).

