## Follow-up Visits

Participants assigned to the immediate treatment arms will be scheduled for follow-up visits at 1 and 3 months after enrollment and then at months 6, 9, 12, 15, 18, 21, and 24 (Table 1, Appendix 3). Study visits for participants assigned to the immediate treatment arm are to be completed + 7 days based on the enrollment visit date. Participants assigned to the delayed treatment arms will be scheduled for follow-up visits at 1 and 3 months after enrollment and then at months 6, 9, 10, 12, 15, 18, 21, and 24 (Table 2, Appendix 3). Study visits for participants assigned to the delayed treatment arm are to be completed + 7 days based on their enrollment visit until their initial dispensing visit . After the initial dispensing visit (month 9), study visits for participants assigned to the delayed treatment arm will be completed + 7 days based on their month 9 visit date. Regularly scheduled evaluations will be made on all participants whether or not they continue to receive study product.

The following procedures are to be performed at all visits unless otherwise specified:

*Epidemiologic/Behavioral Risk Assessment*

- ACASI (3, 6, 9, 12, 15, 18, 21, and 24 months)

Clinical assessment

- Symptom-directed physical examination
- Administration of Adverse Events/Intercurrent Illness Form
- Concomitant Medication Form

*Laboratory assessment:*

- Hematology profile
- Chemistry profile
- Urinalysis
- Blood sample for storage
- Plasma
- Peripheral Blood Mononuclear Cells (PBMCs) (12 months for immediate treatment arms, 21 months for delayed treatment arms only)
- HIV-1 rapid whole blood EIA (3, 6, 9, 12, 15, 18, 21, and 24 months)
- DEXA scan **(SFDPH only: 12 and 24 months for immediate treatment arms, 9 and 24 months for the delayed treatment arms)**
- STI testing
- RPR (12 and 24 months)
- Urine for GC and CT (6, 12, 18, and 24 months)

Standardized HIV risk reduction counseling as per enrollment visit

During the 24 months of the study, additional HIV testing may be requested at any time by study participants, or may be performed as required by the protocol in the case of an indeterminate result or to help determine the timing of HIV infection more precisely.

After participants complete all scheduled study visits, they will be contacted periodically until final study closeout. The purpose of these interim contacts will be to update contact information and to inform participants of the progress of and timeline for completing the study.

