## Behavioral Assessment

Questionnaire Development Systems (QDS) software will be installed at computers at study sites for ACASI use by participants. The ACASI questionnaire will include items on HIV sexual risk behaviors, drug use, depression (55), perceptions of TDF efficacy, adherence, and motivations for study participation. HIV risk behavior data will be obtained at enrollment and at 3 month intervals for the duration of the study. These data include information about unprotected and protected sex with male and female sex partners, sex with HIV seropositive, seronegative, and partners of unknown HIV serostatus, and alcohol and drug use during the past three months. Adherence data will be collected at 3 month intervals (3, 6, 9, 12, 15, 18, 21, 24 months). These adherence items will include a 1 month visual analog scale for dose adherence and timing, (56) questions about reasons for missed doses, possible attitudinal and practical barriers to adherence, the accuracy/truthfulness of self-report, and possible medication sharing.

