## Endpoints

### Primary Endpoints

- The clinical safety and toxicity of TDF will be assessed by the occurrence of moderate and severe clinical and laboratory adverse events in each treatment group. Mild event rates will also be reported.
- The behavioral safety will be assessed by evaluating the change in the reported type and frequency of sexual risk behaviors (e.g. unprotected anal sex, number of sex partners) in each treatment group.

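### The main behavioral comparison does not use the enrollment value of the same behavior; adding it as a covariate would gain precision at no data cost

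*Protocol*

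**What the plan says.** Section 10.2.1 gives the behavioral primary endpoint in terms of change: "The behavioral safety will be assessed by evaluating the change in the reported type and frequency of sexual risk behaviors". Section 10.6 defines the main analysis in terms of level: "The main behavioral safety analysis will compare the overall level of selected behaviors in the immediate and delayed treatment arms", over the first nine months. It names longitudinal binary regression for yes/no responses, to allow for correlation within a man, and claims more than 80% power for a difference of 12 points or more when the delayed-group probability is at least 28%.

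On covariates, the only general statement is in section 10.5: "All safety analyses described will be adjusted for study site and the delayed /immediate treatment group variable".

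The enrollment measurement exists. Section 8.6 says: "HIV risk behavior data will be obtained at enrollment and at 3 month intervals for the duration of the study", with a three-month recall period. Section 6.3 places the ACASI among the enrollment assessments, and product is dispensed once these are complete. The follow-up interviews are scheduled in section 6.8: "ACASI (3, 6, 9, 12, 15, 18, 21, and 24 months". Three of them, at months 3, 6 and 9, fall in the first nine months.

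**The concern.** A man's risk behavior before the study is likely to be among the best predictors of what he reports afterwards. The immediate/delayed variable is the contrast under test in the behavioral comparison, so the stated adjustment leaves site as the only true covariate. A longitudinal model that allows for correlation among follow-up visits does not by itself adjust for baseline.

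Behavioral safety is one of two primary questions, and the worry is an increase in risk-taking. Leaving out a predictive baseline makes the standard error larger than it need be and leaves chance imbalance at enrollment in the estimate. Both make a real but moderate increase easier to miss.

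**Working it through.** **Inputs**
- 400 men in four equal arms (10.3), so n = 200 immediate against 200 delayed.
- Three follow-up interviews, m = 3 (6.8).
- 28% in the delayed arms against 40%, a difference of 12 points (10.6).
- Type 1 error 0.05. Section 10.3 states it for SAEs; two-sided is assumed here.
- Within-man correlation ρ. Section 10.7 gives 0.5, but for adherence. None is stated for behavior, so 0.5 is an assumption and 0.3 to 0.7 is shown.

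**Formulas** (exchangeable correlation, variance relative to one visit)
- Mean of m visits: f = (1 + (m − 1)ρ)/m.
- The same with the enrollment value as covariate: f − ρ².
- Raw change score: f + 1 − 2ρ.
- Power: two-proportion test with n/f men per group.

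**Check of the method.** Applied to two repeated-period adherence figures in 10.7, it gives 85.6% where the protocol states 86% (200 per group, 3 periods, 8% against 16%). It gives 77.7% where the protocol states approximately 80% (100 per group, 5 periods, 8% against 18%).

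**The protocol's own behavioral figure.** At ρ = 0.5, f = (1 + 2 × 0.5)/3 = 0.667 and n/f = 300 per group. The standard error is √(2 × 0.34 × 0.66/300) = 0.0387 under the null and √((0.28 × 0.72 + 0.40 × 0.60)/300) = 0.0384 under the alternative. Then z = (0.12 − 1.96 × 0.0387)/0.0384 ≈ 1.15, so power is 87.5%. Over delayed-group rates from 28% to 60% the minimum is 83.8%, at 44%. The claim of more than 80% reproduces.

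**With the enrollment value as covariate.** At ρ = 0.5 the factor is 0.667 − 0.25 = 0.417. The variance ratio is 0.417/0.667 = 0.625, a cut of 37.5%. This equals 200/0.625 = 320 men per group in place of 200.

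| ρ | Factor: level → adjusted | Variance cut | Difference detectable with 80% power (points) | Power for 12 points |
|---|---|---|---|---|
| 0.3 | 0.533 → 0.443 | 17% | 9.6 → 8.7 | 93.6% → 96.9% |
| 0.5 | 0.667 → 0.417 | 37.5% | 10.8 → 8.4 | 87.5% → 97.6% |
| 0.7 | 0.800 → 0.310 | 61% | 11.8 → 7.2 | 81.0% → 99.5% |

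**Simulation check.** In 3,000 simulated trials with binary correlation 0.5 and 200 per group, power was 89.0% for the level comparison and 97.8% with adjustment. The standard deviation of the estimate fell from 0.038 to 0.031.

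**A raw change score is not the remedy.** At ρ = 0.5 its factor is 0.667 + 1 − 1 = 0.667, so nothing is gained. At ρ = 0.3 it is 0.933, and power for 12 points is 74.8%, against 93.6% for the level comparison.

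**Sensitivity to a weaker baseline.** If the enrollment value correlates c with each follow-up visit, the adjusted factor is f − c². With ρ = 0.5 among follow-up visits but c = 0.3, it is 0.667 − 0.09 = 0.577, a cut of 0.09/0.667 = 13.5%.

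**The case against.** The strongest reply is that nothing stated is wrong. Randomisation makes the level comparison unbiased, and the power claim holds without adjustment. The sentence in 10.5 does not say that no other covariate may be used; it stands in the clinical and laboratory section, and covariate lists are often left to the SAP, which is not shown. All of this stands, and it limits the point to an improvement. What remains is that the protocol does state an adjustment for its safety analyses and describes the main behavioral model, and neither mentions the enrollment value.

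Four stronger readings are tempting, and the documents do not support them.

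- **Dilution by the enrollment record.** A reader might infer that the enrollment interview would be averaged in as an outcome. Section 8.6 gives the questionnaire a three-month recall, so the enrollment interview describes the time before the study. The interviews at months 3, 6 and 9 are the ones that cover the first nine months.
- **Contradiction between endpoint and analysis.** Section 10.2.1 speaks of change and 10.6 of level. The synopsis and the Study Design section both describe a comparison of reported behavior between immediate and delayed arms, which agrees with 10.6. Under randomisation both target the same between-arm difference. This is loose wording.
- **Failed power.** With 160 per group the level comparison has 79.4% power at ρ = 0.5. That needs the full 20% loss by month 9, whereas 10.3 gives 10–20% over the whole study period.
- **A fixed size of gain.** The 0.5 belongs to adherence. The calculation also assumes that enrollment correlates with follow-up as strongly as follow-up visits do with one another, and the last line of the working shows a smaller gain if it does not.

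One technical objection also stands. The variance formula is linear, and adding a covariate to a logistic model changes a marginal odds ratio into a conditional one. The fix has to keep the estimand on the risk-difference scale used in 10.6.

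**Conclusion.** The point holds as a free improvement in precision for a primary safety question. It is not an error, a bias or a failed power claim. Under an exchangeable correlation of 0.3 to 0.7, with 200 per group and three visits, using the enrollment value as a covariate cuts the variance by about 17% to 61%. The direction does not depend on the exact correlation; the size does, and it would be smaller if enrollment predicts follow-up less well than follow-up visits predict one another. The planned 12-point difference is already adequately powered. The practical gain is therefore better sensitivity to increases smaller than 12 points and protection against chance imbalance at enrollment.

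**What to change.** In section 10.6, state that:
- the outcome records of the main analysis are the interviews at months 3, 6 and 9;
- the longitudinal model includes the enrollment value of the same behavior and site as covariates (for count outcomes, the log of the baseline count plus 1), and a raw change score is not used;
- the immediate–delayed contrast is reported as a marginal, standardised risk difference for yes/no behaviors, so that it still matches the 12-point difference on which power is stated.

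Align 10.2.1 by describing the endpoint as the between-arm difference in reported behavior over the first nine months, adjusted for the enrollment value. Section 6.3 could also say outright that the enrollment ACASI is completed before the assignment envelope is opened. The current text implies this, and immediate or delayed assignment is not blinded.

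The cost is protocol or SAP wording and a standardisation step in the analysis program. No new data, visits or participants are needed.

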## Analyses for Study Product Acceptability

The following data will be collected at 3-month intervals regarding acceptability and compliance of usage of the study product:

1) Manual pill count;

2) Electronic cap monitoring (MEMS cap)

Number of times bottle has been opened;

Date/time of each opening;

3) Self -reported adherence behavior and perceptions of study product (ACASI)

Study pill compliance and acceptability will be analyzed using several key measures including the percentage of expected doses actually taken in a given time period; consistency of study product usage over time; and by examining relationships between compliance and key participant demographic, clinical, and psychosocial characteristics.

The major measurement of interest for each three-month period will be the percentage of study product utilized as measured by the MEMS cap device, but pill count and self-reported data on adherence will also be used to address inconsistencies.

The major comparisons of interest for compliance are the differences in usage for the TDF and placebo groups while on study product. Comparisons involving the first 15 months on drug will use all TDF vs. placebo participants while comparisons after 15 months on product will be limited to the participants in the immediate arm. The statistical analyses will utilize longitudinal continuous regression models that can account for within-individual correlation.

Power calculations indicate that while a one-time period with 100 participants per group requires a fairly large difference in compliance (10% vs. 25% noncompliance, power=81%) for power >80%. However, comparisons based on more time periods or 200 participants per group fair considerably better. For example, with 5 time periods and 100 per group (common correlation among time periods assumed to be 0.5) approximate 80% power would be achieved under a true difference of 8% vs. 18%. For 200 participants in each group and 3 time periods, 8% vs. 16% non-compliance in the two groups would have power equal to 86%.

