| Randomization  R  A  N  D  O  M  I  Z  E  Daily TDF  Daily Placebo  No treatment for 9 months, then daily TDF  No treatment for 9 months, then daily Placebo  Site B  Site A  Site C |  |
| Enrollment: | Over 24 months |
| Main eligibility criteria: | Healthy, HIV-1 negative MSM who reported anal intercourse in the last 12 months |
| Study procedures/frequency: | Physical examinations, behavioral risk assessments, and laboratory analyses at screening, baseline, months 1, 3 and then every 3 months through 24 months of study. |
| Test product, dose, and mode of administration: | TDF 300 mg po QD. |
| Criteria for Evaluation | Safety  Clinical and laboratory adverse events  Risk behavior change  Adherence to study drug  HIV antiretroviral resistance |
| Statistical Methods | The primary endpoints are to assess the safety and tolerability of TDF as determined by the proportion of participants with grade 3 or 4 abnormalities (clinical adverse events and laboratory toxicities occurring after treatment initiation), the difference in reported risk behavior between the immediate and delayed treatment arms, and overall rates of adherence. Intent-to-treat analysis will be used. |

GLOSSARY OF ABBREVIATIONS AND DEFINITION OF TERMS

| 3TC | lamivudine, Epivir® |
| --- | --- |
| 3TC/AZT | lamivudine/zidovudine, Combivir® |
| ACASI | audio-computer administered interview |
| AE | adverse event |
| AIDS | acquired immunodefienciency syndrome |
| ALT (SGPT) | alanine aminotransferase |
| AST (SGOT) | aspartate aminotransferase |
| ART | antiretroviral therapy |
| BUN | blood urea nitrogen |
| CAB | community advisory board |
| CBC | complete blood count |
| CBO | community based organization |
| CK | creatine kinase |
| CLIA | clinical laboratory improvement amendments |
| CrCl | calculated creatinine clearance |
| CRF | case report form(s) |
| CRO | contract research organization |
| d4T | stavudine, Zerit® |
| DHHS | Department of Health and Human Services |
| ddI | didanosine, Videx® |
| dL | Deciliter |
| DNA | deoxyribonucleic acid |
| EFV | efavirenz, Sustiva® |
| EIA | enzyme-linked immunosorbent assay |
| FDA | (US) Food and Drug Administration |
| FTC | Emtricitabine |
| g | gram(s) |
| GCP | Good Clinical Practice guidelines |
| HAART | highly active antiretroviral therapy |
| HBV | hepatitis B virus |
| HBsAg | hepatitis B surface antigen |
| HDPE | high‑density polyethylene |
| HIV | human immunodeficiency virus |

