# STUDY DESIGN

This protocol describes a randomized, double-blind, placebo-controlled three-site study to evaluate the safety and tolerability of daily oral TDF among HIV-1 negative MSM.

Four hundred healthy, HIV‑1‑negative MSM will be randomized to one of four treatment arms:

Group 1: TDF 300 mg po QD

Group 2: Placebo po QD

Group 3: No study product for 9 months, followed by TDF 300 mg po QD

Group 4: No study product for 9 months, followed by placebo po QD

Groups 1 and 2 will be referred to as the immediate treatment arms and will receive study product for the entire 24 months of the study. Groups 3 and 4 will be referred to as the delayed treatment arms, and will receive study product starting at 9 months and ending at 24 months, for a total duration of 15 months on study product. For the purposes of this study, a month is considered 30 days. Participants will be stratified by enrollment site.

Participants will be monitored for clinical safety using periodic physical examinations, adverse event reporting, and serial laboratory testing. Given the uncertainty regarding the clinical significance of whole-body duel-energy x-ray absorptiometry [DEXA] findings and their lack of correlation with other clinical data (e.g. fractures), SFDPH site participants will receive DEXA scans at screening and two follow-up visits (at 12 and 24 months in the immediate arm, at 9 and 24 months in the delayed arm), and at the time of study discontinuation, if at least 6 months has passed since the previous scan. Behavioral safety will be primarily assessed by comparing reported risk behaviors between the immediate (pill-groups 1 and 2) and delayed (no pill-groups 3 and 4) treatment arms and will be evaluated by the use of periodic risk behavior assessments via audio computer-assisted self interview (ACASI) and regular laboratory testing for HIV and sexually transmitted infections (STI) including syphilis, *Neisseria gonorrhoeae* (GC), and Chlamydia trachomatis (CT). Additionally, measurements of adherence will be evaluated to determine product acceptability.

Study Schema

R

A

N

D

O

M

I

Z

E

Daily TDF

Daily Placebo

No treatment for 9 months, then daily TDF

No treatment for 9 months, then daily Placebo

Site B

Site A

Site C

Anticipated Timeline

Months

|  | 0-6 | | 7-12 | | | | 13-18 | | | 19-24 | | 25-30 | 31-36 | | 37-42 | |
| --- | --- | --- | --- | --- | --- | --- | --- | --- | --- | --- | --- | --- | --- | --- | --- | --- |

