## Criteria for Suspension of Study Product

Participants will be discontinued from receiving further study tablets for the following reasons:

- Confirmed HIV-1 infection
- Concurrent illness which, in the investigator’s opinion, may be exacerbated by continued product administration, requires treatment which is contraindicated by the protocol, jeopardizes further compliance or follow-up, and may confound the interpretation of adverse events.
- Unacceptable toxicity, as defined in the toxicity management section of the protocol, or which in the judgment of the investigator, compromises the ability to continue study-specific procedures, or is considered to not be in the participant’s best interest.
- Participant request to discontinue for any reason.
- Any clinical condition or social situation that, in the opinion of the investigator, jeopardizes compliance with study product and may confound the interpretation of clinical adverse events
- Non-compliance with at least two consecutive study visits and a clinical or social situation that in the opinion of the investigator would preclude further compliance with study product
- Non-compliance with at least three consecutive study visits and a clinical or social situation that in the opinion of the investigator and CDC would preclude further compliance with study product

Study investigators must make every attempt to continue follow-up visits for the full 24 months whether or not all study medications have been used. Reasons for premature termination from study medication or follow-up visits will be reported on the specific CRF.

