# STATISTICAL CONSIDERATIONS

## Study Design and Analysis Plan Overview

This is a phase II randomized double-blinded placebo-controlled trial to assess the clinical and behavioral safety of daily oral use of TDF among MSM. Four hundred MSM at risk of HIV-1 infection will be recruited from two sites, randomized 1:1:1:1 to one of four treatment arms, and followed for 24 months. Two treatment arms will receive study product (TDF or placebo) for the entire 24 months (the immediate treatment arms) and the other two treatment arms will receive no study product for the initial 9 months and then receive either TDF or placebo for the remaining 15 months. The data analysis will compare clinical and behavioral safety data between the study arms. The analysis will employ the intent-to-treat principle whereby all data from enrolled participants will be analyzed according to the initial randomization assignment regardless of how many doses they received.

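### The main adherence comparison in 10.7 is framed as usage on study product and leaves periods after a permanent stop without a value; this needs reconciling with the synopsis, which puts overall adherence under intent-to-treat

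*Protocol*

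**What the plan says.** Section 10.7 sets the main adherence contrast: "The major comparisons of interest for compliance are the differences in usage for the TDF and placebo groups while on study product". The next sentence adds that "Comparisons involving the first 15 months on drug will use all TDF vs. placebo participants", with later comparisons limited to the immediate arms. One key measure is "the percentage of expected doses actually taken in a given time period". The major measurement for each three-month period is "the percentage of study product utilized as measured by the MEMS cap device".

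The synopsis (Statistical Methods) ends its list of primary endpoints with "overall rates of adherence. Intent-to-treat analysis will be used". Section 10.1 says that "all data from enrolled participants will be analyzed according to the initial randomization assignment regardless of how many doses they received". Section 3 says that "measurements of adherence will be evaluated to determine product acceptability".

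Section 6.11 lists the reasons for ending product. They include "Participant request to discontinue for any reason", unacceptable toxicity and situations that jeopardize compliance. Section 6.10 asks a man who stops permanently to return unused product and to keep attending visits through month 24.

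**The concern.** The reasons for stopping in 6.11 are partly the very things that acceptability is about: the man no longer wants the product, does not tolerate it, or does not take it. If his later periods are absent rather than counted as no use, the remaining men are selected after randomization on something close to the outcome.

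Two consequences follow. The reported percentage describes men still taking product and overstates how much of the assigned product is used. And if TDF differs from placebo mainly in how many men quit, the main comparison can show no difference. Adherence feeds the judgement on whether daily TDF merits further study, so both matter.

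**Working it through.** **1. What happens to a period after a permanent stop.**
- Visits continue whether or not product does (6.8, 6.10), so the man is still on study.
- Unused product goes back and no further tablets are issued (6.10, 6.11). With nothing dispensed and no cap in use, the MEMS percentage has no denominator and no openings.
- Section 10.7 does not say what doses are expected after a stop, or that such a period scores zero. Without a rule, a longitudinal model has no record for it.
- The drop-out checks in 10.5 and 10.6 compare men who left the study with men still on it. Product stoppers are still on it, so those checks do not reach them.
- Section 10.4 tabulates men continuing product separately from men discontinued from product. This supports the literal reading that a stopper is no longer on product.

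**2. The plan's own power figures.** Inputs from 10.7: non-compliance rates, group sizes, number of periods, and correlation 0.5 (stated for the five-period case, assumed here for the three-period case). Two-sided alpha 0.05 is assumed; 10.3 gives 0.05 for the SAE power table. Effective n per group = n·m / (1 + (m − 1)·0.5). Power = Φ(|p1 − p2| / √[(p1(1 − p1) + p2(1 − p2)) / n_eff] − 1.96).

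| Case | n_eff | Computed | Stated |
|---|---|---|---|
| 10% v 25%, n = 100, 1 period | 100 | 81.3% | 81% |
| 8% v 18%, n = 100, 5 periods | 500/3 = 166.7 | 78.4% | about 80% |
| 8% v 16%, n = 200, 3 periods | 600/2 = 300 | 86.0% | 86% |

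The figures reproduce and are not in dispute. The repeated-period cases show that differences of 8 to 10 points are what the plan aims to detect.

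**3. What an on-product comparison can miss.** Let u be the share of doses taken by men on product (the same in both arms) and s the proportion stopped by a given period.

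Overall non-use = 1 − u(1 − s). Arm difference = u(s_TDF − s_placebo). The on-product difference is 0.

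The value u = 0.92 matches the 8% non-compliance in 10.7. The protocol gives no rate for stopping product, so every s below is an assumption. The 10–20% in 10.3 is loss to follow-up, not product stopping.

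| Stopped, TDF v placebo | Overall non-use | Difference | On-product |
|---|---|---|---|
| 10% v 10% | 17.2% v 17.2% | 0 | 8% v 8% |
| 10% v 5% | 17.2% v 12.6% | 4.6 points | 8% v 8% |
| 15% v 10% | 21.8% v 17.2% | 4.6 points | 8% v 8% |
| 20% v 10% | 26.4% v 17.2% | 9.2 points | 8% v 8% |

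Example: 1 − 0.92 × 0.80 = 0.264 and 1 − 0.92 × 0.90 = 0.172. With u = 0.90 the last row becomes 28.0% v 19.0%. Hiding an 8-point difference takes a gap in stopping of 0.08 / 0.92 = 8.7 points. These are figures at one period; averaged over the whole product period the gap is smaller if stops accrue late.

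**4. The reverse effect.** Suppose the true difference is wholly on-product (8% v 16%) and stopping is equal. Counting stoppers as non-users gives 17.2% v 24.4% at 10% stopped and 26.4% v 32.8% at 20%. With n = 200 and 3 periods, power falls from 86% to 58% and 40% (pooled-variance form of the formula above). If stoppers simply leave, it falls to 82% and 77%. Neither version serves both questions.

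**The case against.** The strongest reply is that the phrase means scheduled time. The sentence after it brings in all TDF and placebo participants for the first 15 months, which is the delayed arms' assigned duration. Section 3 uses the same expression for that scheduled 15 months, and 10.5 says participants are followed for at least 15 months on product, which can be true of everyone only as scheduled time. On that reading the phrase merely removes the delayed arms' nine product-free months. This is a fair reading. It still leaves a post-stop period without a MEMS value or a definition of expected doses, so it narrows the point without closing it.

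A reader might infer that the protocol has a rule removing men who quit and so breaks intent-to-treat outright. The documents do not support that. No sentence removes them, and comparing usage by randomized arm reassigns no one. Adherence is a secondary objective (section 2) and a secondary endpoint (10.2.2); only the synopsis sets it directly beside intent-to-treat. The SAP, which was not at hand, may define the handling.

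Quitting is also not invisible. Section 10.4 tabulates disposition and reasons for discontinuation, and 10.5 lists adverse events leading to it. These tables do not enter the adherence comparison.

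On size, the protocol's background (1.2, Safety) reports comparable adverse event rates for TDF and placebo, which points away from a large gap in stopping. Against that, study 903 found that 6% (TDF) v 2% (stavudine) met its definition of a BMD decrease at 48 weeks, and a BMD loss above 5% stops product here (6.5). Both come from HIV-infected patients and are only indicative.

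Finally, scoring every stop as zero is debatable. Some stops are required by the protocol (6.5, 6.6.1, 9.6), and DEXA is done at one site only. This stands, and it is why zero-scored use should not be the sole comparison.

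**Conclusion.** The point holds as an ambiguity with a practical consequence. By its literal wording, and because no product or cap data exist after a permanent stop, the comparison in 10.7 leaves post-stop periods out. The synopsis promises overall adherence under intent-to-treat. The two need reconciling.

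The size cannot be fixed from the protocol. If stopping differs by about 9 points between arms with equal use on product, a difference as large as the smallest one in the plan's power examples (8 points) can go unseen. A 5-point gap in stopping hides about 4.6 points. With equal stopping no arm difference is hidden, but overall use is overstated: at 10% stopped it is 82.8% rather than 92%, at 20% it is 73.6%. All of this assumes 92% use on product in both arms and assumed stop rates. The change is worth making before unblinding because it is cheap, although the endpoint is secondary in the body of the protocol.

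**What to change.** In 10.7, state that in the intent-to-treat adherence comparison the on-product phrase means the assigned product period: months 0–24 for the immediate arms and 9–24 for the delayed arms. Then report by randomized arm:

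- (a) the percentage of scheduled doses taken over that period, with periods after permanent discontinuation counted as no use;
- (b) the on-product percentage, as now planned;
- (c) the proportion still on product over time, with reasons for stopping.

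Add a sensitivity version of (a) that treats all protocol-required stops alike (HIV infection, PEP, toxicity rules, BMD loss) as not scheduled. Align the synopsis and 10.7 with this wording.

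The cost is analysis text and a few tables. Reasons for stopping are already recorded on a CRF (6.11), and the discontinuation visit and dispensing records help date the stop (6.10, 11.1). No visit, procedure or treatment rule changes. The downsides are a lower overall adherence figure and less power in (a) than in (b) for a purely on-product difference, which is why both are reported.
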